## Abstract

**Introduction:**

HIV prevalence and sexual risk have been estimated very high for transgender people. However, the limited sampling and data collection methods used in current research on transgender people potentially led to overrepresentation and generalisation of people at risk for HIV. Current HIV prevalence estimates in transgender populations are generalised from studies mainly focusing on transgender women engaging in sex work. Moreover, studies focusing on non-binary people, who identify with a broad range of identities beyond the traditional male and female gender identities, are scarce.

**Objectives:**

To estimate the HIV prevalence rate in the Flemish and Brussels (Belgium) transgender population, including transgender women, transgender men and non-binary people, and to identify the associated risk factors.

**Methods:**

In this community-based cross-sectional study, self-identified transgender and non-binary (TGNB) people will be recruited through a two-stage time-location sampling approach. First, community settings in which TGNB people gather will be mapped to develop an accurate sampling frame. Secondly, a multistage sampling design is applied involving a stratification based on setting type (healthcare facilities vs outreach events), a selection of clusters by systematic sampling and a simple random selection of TGNB people within each cluster. Participants will complete an electronic self-reported survey to measure sociological, sexual and drug-using behaviors (risk factors) and oral fluid aliquots will be collected and tested for HIV antibodies. Logistic regression models will be used to evaluate risk factors independently associated with HIV infection. The presented study is registered at ClinicalTrials.gov (NCT04930614).

**Discussion:**

This study will be the first to investigate the HIV prevalence rates and associated risk behaviors in an accurate representation of the TGNB population in a Western European country. The findings will globally serve as a knowledge base for identifying subgroups at risk for becoming infected with HIV within TGNB people and to set up targeted prevention programs.

## Introduction

Globally, 0.7% of all adults aged 15 to 49 years are living with HIV [1]. The prevalence of HIV infection is estimated at 0.4% and 0.17% in Europe and Belgium, respectively [2]. The World Health Organisation (WHO) has listed five key populations at risk for HIV: men who have sex with men (MSM), sex workers, people in prisons or closed settings, people who inject drugs and transgender people [3]. Indeed, over the past 15 years, HIV prevalence has been estimated high for transgender people.

Transgender people are people who do not or to a lesser extent identify with their birth-assigned gender: transgender women are people who were assigned male at birth (AMAB) but identify on the female spectrum; transgender men are people who were assigned female at birth (AFAB) but identify on the male spectrum. Those who do not identify as binary trans, but who identify between, outside and beyond the gender binary are referred to in this article as non-binary people.

A global HIV prevalence rate of 19.1% has been calculated among transgender people, based on 39 studies in 15 countries [4]. A meta-analysis based on 29 US-based studies estimated a self-reported HIV prevalence rate of 11.8% and laboratory-confirmed HIV prevalence rate of 27.7% [5]. A recent update of this meta-analysis, based on 88 studies published between 2006 and 2018 calculated an overall HIV prevalence of 13.7% and an HIV prevalence of 18.8% among transgender women [6]. Furthermore, this study calculated a self-reported history of sexually transmitted disease (STD) diagnosis rate of 21.5%.

Most studies on HIV identify high rates of sexual risk behaviors among transgender people, such as unprotected intercourse, having multiple partners and having sex while drunk or high [4]. Engagement in sex work is also frequently reported, for transgender women as well as for transgender men. The meta-analysis of Becasen et al [6] reports that 31% of all transgender people had a history of sex work: 37.9% of all transgender women and 13.1% of all transgender men. The engagement of transgender people in sex work is frequently attributed to discrimination on the job market, leading to economic marginalisation and forcing transgender people in sex work to survive [7]. Discrimination and rejection have been significantly associated with sexual risk behaviour [8]. Stigma and discrimination may lead to lower self-esteem, mental health issues and the need for acceptance and affirmation from others, which may lead to lower self-efficacy to negotiate safe sex [9]. As such, transgender people experience multiple and overlapping vulnerabilities which have an influence on their health.

However, although HIV prevalence is considered high among transgender populations, prevalence rates also tend to vary widely. A recent systematic review shows that prevalence rates range between 0% and 49.6% across studies [10]. Hence several researchers have been critical towards current HIV research in transgender people more specifically regarding the samples used as well as the lack of accounting for intragroup variation, and the lack of inclusion of community perspectives [11, 12].

### Sampling issues

Oversampling of transgender people at high risk for HIV appears to be common: a lot of studies are focused on transgender women or (female) transgender sex workers [4, 10–12]. For example, the recent systematic review of van Gerwen et al. [10] included 25 studies. All of these studies included transgender women but only 9 included data on transgender men, often in small samples. A lot of transgender HIV research has been conducted in sexual health clinics and community centres in large urban areas, resulting in samples of transgender people at high risk for HIV [4, 10–12].

Obtaining a generalizable sample of transgender people is difficult due to a lack of reliable up-to-date information regarding the number and the proportion of TGNB people in the general population [13]. Hence, transgender health research is based on either clinical samples of transgender people attending specialized transgender healthcare clinics, or on convenience community samples. Clinical samples are limited since a significant proportion of the transgender community either has no access to transgender healthcare or does not want or need medical interventions. Findings from the recent European Union Agency for Fundamental Rights (FRA) study show that up to 65% of all Belgian transgender respondents and 72% of all European transgender respondents had not undergone any medical intervention to change their body in order to match their gender identity [14]. Studies using broad convenience community samples usually recruit via LGBT+ (lesbian, gay, bisexual, transgender and other) or specific transgender organisations, whereas not all transgender people are connected to such organisations–certainly not years after transitioning. The FRA study for instance shows that 72% of all Belgian transgender respondents and 76% of all European transgender respondents are not actively involved in an LGBT+ organisation [14]. Some subgroups of the transgender community remain largely invisible, for instance those who have not yet come out as being transgender, those who live ‘stealth’ or people who are homeless [15].

It becomes clear that as long as gender identity is not taken into account in general population research, obtaining a generalizable sample of transgender people is nearly impossible [16–18]. Some recent studies have attempted to obtain more representative samples of transgender people. A large online sample of US-based transgender people shows for instance a self-reported HIV rate of 2.2%, which is much lower than estimates cited in other studies using self-reported data [19]. The recent meta-analysis of Becasen et al. [6] indeed shows relatively lower estimates than previous meta-analyses, which does not indicate a decrease in HIV infections but more likely reflects research slowly beginning to include transgender people from locations and backgrounds that might be more representative of the overall transgender population [6].

### Intra-group variation

Although HIV prevalence has been estimated relatively high for transgender women (0–49.6%), HIV prevalence is estimated much lower in transgender men, ranging between 0 and 8.3% [5, 6, 10], however few studies include or specifically focus on this subpopulation. Having (cisgender) female sexual partners and lower participation in sexual risk behavior are suggested explanations for this lower HIV prevalence, but more research is warranted [6]. Most current HIV research remains highly heteronormative, focusing on transgender women engaging in receptive anal intercourse with cisgender men. Having sex with cisgender men, regardless of the gender identity of the person itself, has indeed been shown to be a high risk factor for transgender people [19]. However, transgender women with female partners as well as transgender men with male partners and transgender people with transgender partners have been largely ignored in current HIV research. A Canadian study reported that within their sample of transgender men (n = 227) only 34.3% were identified as heterosexual, and 31% had a (cisgender or transgender) male partner during the past year [20]. Of these transgender men who are gay, bisexual or MSM (GB-MSM), 9.2% had high risk sexual intercourse, 14.1% had more than 5 sex partners during the past year and 15.8% had ever been engaged in sex work. Reviews of MacCarthy et al. [12], Van Schuylenbergh et al. [11] and Van Gerwen et al. [10] further show that current sociological and serological research also remains binary and cisnormative. Research including non-binary transgender people, who identify with a broad range of identities that lay between or beyond the traditional male and female gender identities, is scarce to non-existent. Furthermore, prevalence rates seem to be higher for transgender women of color: the US-based systematic review of Herbst et al. [5] calculated a HIV prevalence of 56.3% for black, 16.1% for Hispanic and 16.7% for white transgender people. Compared to white transgender women, black and Hispanic transgender women seem to be more involved in sex work and report more unprotected receptive anal intercourse [21].

In summary, intra-group variation within the transgender population is clear, but often overlooked, and perspectives that account for the intersection of different identities still lack in current transgender HIV research.

### Community perspectives

In the past, research involving transgender people has been pathologizing, stigmatizing and even transphobic [22, 23]. Researchers have for instance systematically misgendered transgender people, regarded ‘transgender’ as a category of sexuality and conflated lesbian, gay, bisexual and transgender populations [22]. Specifically for HIV research, categorising transgender women as MSM was, and often still is, a common practice [24]. This has led some transgender people to distrust researchers investigating transgender health or identities [24]. Furthermore, lack of transparency in communication by researchers, feeling used for research and not hearing about findings from research they participated in are important issues raised by transgender people, often leading to research mistrust [15, 24]. This is why ‘community involvement’ is considered an important aspect of ethical research in transgender populations [22, 24–27]. Furthermore, researchers stress a need for multiple modalities and methods to reach different subsets of the transgender community, preferably using peer recruitment techniques and ensuring transgender participation in advisory groups, to make sure hard-to-reach groups are included too [15, 24].

Overgeneralization of findings to the transgender population as a whole still persists, and should be critically investigated. Studies have been limited to specific regional and contextual settings, such as large urban centres in North-America (San Francisco, Los Angeles), although the social as well as the legal context for transgender people greatly differs between countries and regions. Unpublished data from a large European study on transgender health suggests that self-reported HIV prevalence in European transgender people is estimated lower than the prevalence rates often cited in the mainly US-based literature, around 1.6% [28]. However, European peer-reviewed articles that provide actual and current information on HIV prevalence and sexual health in a representative sample of transgender people are not available.

With this research protocol we present a study investigating HIV prevalence in the heterogenous transgender population in Flanders and Brussels (Belgium). In contrast to previous transgender HIV research, this study specifically aims to include non-binary transgender people. This is why the term ‘transgender and non-binary (TGNB) people’ is further used to describe the study population.

## Objectives

This protocol describes the setup of a study aiming to provide a first HIV prevalence estimate for a representative sample of TGNB people residing in a Western European country by combining state-of-the-art epidemiological and sociological methods. By applying a Community-Based Participatory Research (CBPR) and Time-Location Sampling (TLS) approach, this study will allow us for the first time (i) to qualitatively build a sociological map of community settings in which TGNB people congregate for building a sampling frame, (ii) to determine the prevalence of HIV infections in the Flemish and Brussels TGNB population and (iii) to identify associated (sexual) risk factors. The study hypothesis is threefold: (i) social networks and settings where TGNB people may congregate exist, (ii) TGNB people have relatively high rates of HIV infection but differences in HIV prevalence across this heterogeneous population may exist and (iii) the HIV prevalence is mainly determined by sexual risk behavior.

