#### Statistical analysis plan

The proportion of HIV infection and 95% confidence interval will be estimated adjusting for clustering and unequal probability of selection. TGNB people who visited sites more frequently had a higher probability of selection in the study. (Individual) weighting factors will be calculated based on the attendance information provided by the participant to adjust for this unequal selection probability. Moreover, the probability of accepting participation and the sampling fraction (number of participants out of total number of eligible attendees at the cluster) will also be taken into account. One can expect that the real number of attendees at outreach events may deviate from the expected number used for the systematic sampling procedure. The actual number of eligible TGNB persons will always be reported in the data collection form and, if needed, weighting factors will be calculated to correct for the potential deviation in sampling probability.

Socio-demographic and geographic characteristics, sexual and drug-related risk factors of the sample will first be summarized by descriptive statistics. Logistic regression models taking into account clustering and using the sampling weights (being inversely proportional to the selection probability) will be fitted to calculate the odds ratio (OR) and 95% CI for each possible risk factor. Nine variables will be queried to map sexual risk behavior among TGNB people and three variables deal with the use of needles or risky blood contacts in the past. Depending on the number of TGNB people with HIV infection, construction of a multivariable model will be considered to estimate adjusted OR (aOR). After constructing a logistic regression model including all confounding factors (e.g. age or country of birth) that had a P<0.05 in univariate analysis, the significant risk factor(s) will then be separately added as explanatory factors to estimate aOR when deemed appropriate. Statistical analyses will be undertaken using the package ‘survey’ in RStudio to fit the above logistic regression models. Marginal models in the ‘survey’ package focus on the population mean response, averaged over all clusters, taking into account clustering and the sampling weights. Sensitivity analyses might be performed to assess the impact of e.g. potential protocol violations on the robustness of the results.

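### Hypothesis (iii) claims that sexual risk behaviour is the main determinant of HIV prevalence, but significant odds ratios for single behaviours, which are all the plan provides, cannot establish that

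*Protocol article*

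**What the plan says.** The Objectives section of the protocol article separates three aims from a threefold hypothesis. The third aim is to identify associated (sexual) risk factors. The third hypothesis goes further: "the HIV prevalence is mainly determined by sexual risk behavior". No measure or criterion for *mainly* is given.

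The Statistical analysis plan section first describes the risk factors. It then specifies logistic models, weighted and allowing for clustering, to "calculate the odds ratio (OR) and 95% CI for each possible risk factor". On the sexual exposures it says "Nine variables will be queried to map sexual risk behavior among TGNB people". Another three cover needle use and risky contact with blood. A multivariable model is only to be considered, depending on the number of HIV cases. If it is built, the confounders go in first, and "the significant risk factor(s) will then be separately added as explanatory factors to estimate aOR when deemed appropriate".

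The Sample size section sizes the risk-factor analysis as a comparison of two proportions. The Discussion states that exposure is recalled over the past 12 months.

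**The concern.** The hypothesis concerns predominance, and the analysis concerns association, one behaviour at a time. Nothing in the article combines the nine sexual variables, combines the three needle or blood-contact variables, or compares the two groups. An odds ratio measures how strongly an exposure goes with infection. It does not say how many infected people had the exposure, or how far several behaviours occur in the same people.

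What is at stake is the wording of the conclusion. The abstract says the findings will be used to identify subgroups at risk and to set up targeted prevention, and the Dissemination section stresses avoiding harmful use of the results. A report that HIV in this population is mainly determined by sexual behaviour would be a strong statement, and the planned output could not carry it.

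**Working it through.** **1. The plan's own figure.** Inputs from Sample size and Table 1: p0 = 0.06 with risk behaviour, p1 = 0.005 without, r = 3, z values 1.96 and 0.8416, design effect 2.36.
- Pooled p = (0.06 + 3 × 0.005)/4 = 0.01875.
- n = [1.96 × √(4 × 0.01875 × 0.98125) + 0.8416 × √(3 × 0.06 × 0.94 + 0.005 × 0.995)]² / (3 × 0.055²) = 85.9, rounded up to 86.
- Total = 4 × 86 × 2.36 = 812, as stated.

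The other three rows reproduce within 3%. The sizing is sound for detecting an association. It does not address a share of the prevalence.

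**2. What that odds ratio says about a share.** OR = (0.06/0.94)/(0.005/0.995) = 12.7, and RR = 0.06/0.005 = 12. With pe the proportion exposed:

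excess fraction = pe(RR − 1)/[1 + pe(RR − 1)]

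overall prevalence = pe × p0 + (1 − pe) × p1

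| pe | Source | Excess fraction | Overall HIV |
|---|---|---|---|
| 25% | r = 3 | 2.75/3.75 = 73% | 1.9% |
| 10% | assumption | 1.10/2.10 = 52% | 1.05% |
| 5% | assumption | 0.55/1.55 = 35% | 0.78% |

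The same odds ratio fits a majority and a minority of cases. The fraction exceeds 50% only when pe > 1/(RR − 1). For the four Table 1 rows (RR 12, 9, 35, 6) that means 9.1%, 12.5%, 2.9% and 20% exposed.

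**3. A case at the planning prevalence.** The low-exposure rows above sit well below the 3% used for sample size. Take instead 6% versus 2% with 25% exposed (the 2% is an assumption chosen to give 3% overall): 0.25 × 0.06 + 0.75 × 0.02 = 0.03.
- OR = (0.06/0.94)/(0.02/0.98) = 3.1.
- Excess fraction = 0.25 × 2/(1 + 0.25 × 2) = 33%.
- Effective size = 1322/2.36 = 560, that is 140 exposed and 420 unexposed. Power (normal approximation, two-sided 5%) = Φ[(0.04 − 1.96 × 0.01665)/0.02120] = 0.64.

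So a significant sexual odds ratio is more likely than not here, although only a third of cases are in excess.

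**4. Overlap.** Fractions for separate behaviours cannot be added. If two behaviours were reported by the same 25% of people, each would have a fraction of 73%, and the sum would be 147%. A joint share needs a combined exposure, and adding factors separately does not produce one.

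**The case against.** The strongest reply is that the working aim is association. The objectives, the abstract and the sample size all say so, and the odds ratios serve that aim. The hypothesis may be loose framing, and *mainly determined* could mean the strongest determinant, for which odds ratios are relevant. This stands in part. It limits the point to the wording of the hypothesis and what may be concluded from it. Even on the strongest-determinant reading, however, no comparison between sexual and other exposures is planned.

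A reader might infer that the hypothesis can be neither supported nor refuted. That goes too far: null odds ratios for every sexual variable would speak against it. A reader might also infer that the investigators will count significant results, nine chances against three. With independent 5% tests and no true association, at least one hit has probability 1 − 0.95⁹ = 37% against 1 − 0.95³ = 14%. But the article states no such counting rule, and the sexual behaviours it lists plainly overlap, so independence is doubtful. The point does not rest on this.

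Exposure frequencies will be described, so a crude fraction per behaviour could be derived later. None is planned, and overlap would still prevent a joint share. The effective size of 560 is also pessimistic, since the Sample size section expects a smaller design effect for risk factors.

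Details are commonly left to a fuller plan. Here, though, the article itself states both the hypothesis and the model-building rule, and the two do not match.

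**Conclusion.** The point holds as a mismatch between one stated hypothesis and the stated analysis. Significant odds ratios for single behaviours cannot establish that sexual behaviour accounts for most of the prevalence. An odds ratio of 12.7 is compatible with fractions from 35% to 73% as exposure runs from 5% to 25%, and an odds ratio of 3.1 at the planned prevalence goes with 33%. Exposures other than 25% are assumptions, and the 10% and 5% examples imply about 1% HIV overall, or roughly 14 and 10 cases in 1322. They illustrate the principle and do not forecast this study.

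The documents do not support a demand that an attributable fraction be made the test of the hypothesis. Exposure over the past 12 months set against prevalent infection makes *determined* doubtful however the share is computed, and the precision is poor. In simulations with 140 exposed and 420 unexposed, the central 95% of estimates ran from about 33% to 100% around a true 73%, and from about 0% to 67% around a true 33%. A rule requiring the lower limit to exceed 50% would be met in about 30% of runs with a bootstrap interval when the truth is 73%, and in under 1% with a log-scale delta interval.

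**What to change.** 1. In Objectives, reword hypothesis (iii) to say that HIV infection is associated with sexual risk behaviour.
2. In the Statistical analysis plan, add a weighted, design-based descriptive table with 95% confidence intervals. It should give the percentage of HIV-positive and of HIV-negative participants reporting any of the nine sexual variables, any of the three needle or blood-contact variables, both, or neither. Use main-questionnaire items where possible: some drug, condom and transfusion items are in the follow-up questionnaire, for which the protocol expects a relatively low response.
3. State that odds ratios alone will not be read as showing that sexual behaviour is the main determinant.
4. If an attributable fraction for the two composites is reported, label it exploratory, give its interval and the 12-month recall limit, and attach no 50% decision rule.

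The cost is a few lines of text and code and a softer claim. If main-questionnaire items are used, no new data are needed. The prevalence estimate and the sample size do not change.
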